### Intervention and control groups

#### **A) VR-based MBI group (Intervention group)**

Upon enrolment in the study, participants assigned to the VR-based MBI group will be invited to a briefing session at Lingnan University. The session will take place in a quiet room with suitable lighting and air conditioning. Following the participants' written informed consent, they will be introduced to the VR-based MBI user manual, VR technology after completing a pre-test survey.

During the briefing session, participants will download the VR-based MBI app developed by our research team and familiarize themselves with wearing the JAPAN JTSK 6th generation upgraded version of 3D virtual reality glasses. They will engage in a 5-10 minute exercise within the VR environment, giving them the opportunity to explore different natural sceneries provided

in the app. This exercise aims to acclimate participants to the VR technology and allow them to select environments for their mindfulness practice at home. Participants will be provided with the VR glasses to take home and practice mindfulness for approximately 10-15 minutes daily over the next eight weeks. The app will record their practice time for further analysis. Weekly telephone follow-ups will be conducted to address any questions or concerns, and reminder messages will be sent once a week.

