### Randomisation

Eligible participants will be randomly assigned into three groups: A) VR-based MBI (Intervention group) B) audio-based MBI group (control group) and C) Usual care group (Waitlist control group). Individual randomization using serially numbered opaque sealed envelopes (SNOSE) will be used to ensure that the allocation sequence is concealed from participants before the group allocation. The PA will prepare about 90 identical, opaque, sealed A5-sized envelopes, with a unique three-digit serial number on the cover of each envelope as an identifier. One-third of the envelopes will contain the action plan for the intervention group, another third the action plan for the audio-based MBI group, and the remaining envelopes the action plan for the waitlist control group. The intervention materials will be inserted into the envelopes, which will be sealed, shuffled, and numbered. Once a participant consents to participate in the study, the RA will open one envelope according to the sequence of the serial number and assign the participant to a treatment condition based on the action plan. No participants will be blinded to the given interventions.

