#### **C) Usual care group (Waitlist control group)**

The third group will be the waitlist control group, who will not attend any briefing session or engage in mindfulness-based interventions during the pilot period. Instead, they will receive usual care and services provided by community service centres. No additional or new intervention will be provided to them during the study period. We will provide the VR-based MBI to the waitlist control group participants after they have completed the control period.

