#### Assessment

Timeline of overall evaluation plan on intervention effectiveness is shown in Figure 2. All participants will complete a 30-minute face-to-face survey comprising a set of assessment on psychological stress, well-being, and other relevant outcomes before the intervention and after the 8-week intervention. To minimize the survey effect and to assess the long-term effects, we will also conduct a phone interview as a follow-up survey at two months after the intervention.

The VR-based MBI group will also participate in two face-to-face, 60-minute, audio-recorded focus group discussions—one immediately after the intervention and another at the two-month follow-up—to provide in-depth feedback on their experience with the intervention. These discussions will help us understand the impact of the VR-based MBI and identify any potential benefits or challenges.

All face-to-face surveys and focus groups will be organised and taken place at Lingnan University.

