## **Ethics consideration**

### Major ethical issues

The study follows the Declaration of Helsinki on medical protocol and ethics. Ethics approval will be obtained from the HKU/HA HKW Institutional Review Board (HKU/HA HKW IRB). Participants are voluntary to join the study. A written informed consent, which will include the research title, purpose, explanation of the research, and the procedures of the study, will be obtained from each eligible participant. Risks and benefits are also explained clearly to the participants. Participants have the right to withdraw from the study at any time. They will be protected from discomfort and harm during the study. Further, anonymity and confidentiality of the participants will be strictly protected.

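### The Protocol leaves open whether written consent and the baseline survey come before or after allocation, so caregivers might decline once they know their arm

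*Protocol*

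**What the plan says.** Four places in the Protocol bear on the order of consent, baseline and allocation.

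- **Randomisation:** "Once a participant consents to participate in the study, the RA will open one envelope according to the sequence of the serial number". Consent comes first, but the section does not say whether this is the written consent. It adds: "No participants will be blinded to the given interventions".
- **A) VR-based MBI group:** on enrolment, "participants assigned to the VR-based MBI group will be invited to a briefing session at Lingnan University". After a description of the room, the text says that, following their "written informed consent, they will be introduced to the VR-based MBI user manual, VR technology after completing a pre-test survey".
- **C) Usual care group:** these are caregivers "who will not attend any briefing session". The section names no consent step. Section B) gives the audio arm a briefing but names no consent step either.
- **Major ethical issues:** written informed consent "will be obtained from each eligible participant". Its timing relative to allocation is not given.

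Under Assessment, all participants complete the face-to-face survey before the intervention, and "All face-to-face surveys and focus groups will be organised and taken place at Lingnan University". Under Results analysis, participants who are lost to or refuse follow-up are treated as showing no change.

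**The concern.** In an unblinded trial, the signature should come before the arm is known. Otherwise a caregiver who dislikes the allocation can decline to sign. Written consent is required, so that person cannot then be surveyed, and a randomised caregiver drops out before any data exist. Reasons for declining could plausibly differ between arms, such as unease with a headset in one and having to wait in another.

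Two things would be at stake. The first is the comparability of the arms in the efficacy contrasts. The second is the pilot's own feasibility output: Indicators and targets lists reach and retention, and both need a clear denominator. The Protocol plans about 90 envelopes for 90 participants and gives no rule for an envelope opened for someone who then declines.

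**Working it through.** **Order of events, section by section**

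| Section | Order stated | What is left open |
|---|---|---|
| Randomisation | consent, then envelope | whether this consent is written |
| A) VR arm | assigned, invited to briefing, written consent and pre-test, VR introduction | whether the consent clause refers back |
| B) Audio arm | briefing | when consent and T0 occur |
| C) Waitlist arm | no briefing | when consent occurs |
| Major ethical issues | written consent from every eligible person | timing |

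No section identifies the consent in Randomisation with the written consent in the VR-arm section. The VR-arm section, taken in sequence, puts both the signature and the pre-test survey after assignment.

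**What the analysis rule can recover.** The no-change rule carries a baseline value forward. A caregiver who leaves before the pre-test has none, so the rule cannot keep that person in the analysis.

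**Size.** The Protocol gives no figure to reproduce, so this is an illustration on assumed inputs. Let p be the share of one arm declining after assignment and g the gap in outcome between stayers and decliners, in SD. The mean of the stayers then differs from the mean of the whole arm by p × g. For two arms with the same g, the bias in the contrast is (p1 − p2) × g.

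With no refusal in the comparison arm (p2 = 0):

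- p = 0.05, g = 0.3: 0.05 × 0.3 = 0.015 SD
- p = 0.10, g = 0.5: 0.10 × 0.5 = 0.05 SD
- p = 0.20, g = 0.8: 0.20 × 0.8 = 0.16 SD

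With refusal of 20% against 5% and g = 0.8: (0.20 − 0.05) × 0.8 = 0.12 SD. With equal refusal and the same g: 0.

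Against the effect sizes of 0.4 to 0.54 in the sample-size paragraph, the range runs from 0.015/0.54 = 3% to 0.16/0.40 = 40%.

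**Lost numbers.** At 20% refusal in one arm, 0.20 × 30 = 6 caregivers are lost, leaving 24 against 30. At an assumed two-sided 5% level, power goes from 0.34 to 0.31 for an effect of 0.4, and from 0.55 to 0.51 for 0.54. Selection matters more here than the loss of numbers.

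**The case against.** The strongest reply is that the order is already right where it belongs. Randomisation puts consent before the envelope, and the ethics section asks for written consent from eligible, not assigned, people. The VR-arm section opens with participants already enrolled, so its consent clause may simply look back to a signature already given. The waitlist arm has no briefing, which makes best sense if everyone signs at a common earlier step. Figure 1, the flow diagram, was not available here and may settle the matter.

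Much of this stands. A reader might infer that the trial takes oral agreement, opens the envelope and collects signatures afterwards. The Protocol mentions no oral or provisional consent, so that sequence is conjecture. A reader might also infer that every arm contrast is biased. That needs more than the order of signing: losses must act differently across arms, and decliners must differ from stayers in outcome. The planned mixed model includes a group-by-time interaction, so a stable difference in level would largely cancel and the gap that matters is one in change.

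It is also fair that an earlier signature would not stop an unblinded caregiver from withdrawing after the envelope. That argues for taking the T0 survey before allocation too, so that such a person at least has a baseline value.

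The reply does not remove the inconsistency. No sentence says that the consent before the envelope is the written one, and the VR-arm section in its plain order says otherwise. It also puts the pre-test survey after assignment, which the backward-looking reading of the consent clause does not explain.

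**Conclusion.** The Protocol is inconsistent on whether written consent and the baseline survey precede allocation, and it should be reconciled. It does not show that consent is taken after allocation, and it does not show that the results will be biased. If a site follows the VR-arm order, post-allocation refusal before any baseline can bias the contrasts and blur the recruitment and retention denominators.

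The size is unknown. About 0.02 to 0.16 SD follows from assumed refusal of 5% to 20% in one arm only and an assumed gap of 0.3 to 0.8 SD. It is zero if refusal does not differ by arm and the gap is the same. None of these inputs is in the Protocol. The case for acting rests on the low cost of the correction, not on a demonstrated bias.

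**What to change.** Reconcile Randomisation and sections A), B) and C) to one order for all three arms: written informed consent covering all arms, then the T0 survey, then the envelope. State in Randomisation that the consent meant there is the written one. Remove the consent and pre-test clauses from the VR briefing. Count everyone whose envelope is opened as randomised, and report by arm those who leave before the briefing or, for the waitlist arm, before first contact. Check that Figure 1 shows the same order.

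The cost is mainly rewording. Every participant already attends a face-to-face T0 survey at Lingnan University, so no visit is added. For the VR and audio arms, the T0 survey and the envelope must come before the briefing. They can be at the same visit, provided staff are ready to run whichever briefing the envelope calls for.

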| Quantitative assessment | T0 face-to-face survey
Site: Lingnan University                                                                                                                                                                                                                                                                 | T1 face-to-face survey
Site: Lingnan University                                                                                                                                                                                                                                                                                                   | T2 Phone survey                                                                                                                                                                                                                                                       |
| Assessment tool                | 
 
• Basic information (pre-test only)
 
• DASS21
 
• EQ-5D-5L
 
• CZBI
 
• EQ-5D-5L-proxy (Quality of life of care recipients)
 
• Five Facet Mindfulness Questionnaire
 
• ONS4
 
• Relationship Closeness Scale
 
 | 
 
• DASS21
 
• EQ-5D-5L
 
• CZBI
 
• EQ-5D-5L-proxy (Quality of life of care recipients)
 
• Five Facet Mindfulness Questionnaire
 
• ONS4
 
• Relationship Closeness Scale
 
• Treatment Acceptance/Adherence (post-test for VR group only)
 
 | 
 
• DASS21
 
• EQ-5D-5L
 
• CZBI
 
• EQ-5D-5L-proxy (Quality of life of care recipients)
 
• Five Facet Mindfulness Questionnaire
 
• ONS4
 
• Relationship Closeness Scale
 
 |

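### As written, the envelope is opened at consent and the baseline survey follows, so T0 self-reports can be given with the arm known (explicit for VR, inferred for audio and waitlist)

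*Protocol*

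**What the plan says.** **Allocation.** Protocol, Randomisation: "Once a participant consents to participate in the study, the RA will open one envelope according to the sequence of the serial number", and assigns the arm from its contents. The same section adds: "No participants will be blinded to the given interventions". It mentions no survey between consent and envelope.

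**T0 in the VR arm.** Protocol, Intervention and control groups, A): "participants assigned to the VR-based MBI group will be invited to a briefing session at Lingnan University". There, following written informed consent, "they will be introduced to the VR-based MBI user manual, VR technology after completing a pre-test survey".

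**T0 in the other arms.** Section B (audio) describes a briefing but does not time T0. Section C describes the waitlist group as one "who will not attend any briefing session or engage in mindfulness-based interventions during the pilot period" and does not time T0 either.

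**T0 for everyone.** The Assessment section has all participants complete a face-to-face survey on psychological stress, well-being and "other relevant outcomes before the intervention and after the 8-week intervention". Figure 2 gives the mode and place: "T0 face-to-face survey Site: Lingnan University". T0 is thus tied to the start of the intervention and not to randomisation.

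**Blinding.** The Blinding section covers the research assistant who collects post-test data. It does not mention T0.

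**Use of T0.** Results analysis specifies paired t-tests of pre-post change, between-group t-tests, and a linear mixed model with group, time and their interaction. Participants lost at follow-up are counted as unchanged.

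**The concern.** A baseline is safe from allocation effects only if it is recorded before anyone knows the allocation. Both primary measures here are self-reports. A caregiver who has just learned that she will receive the VR programme, or will wait for it, may describe her distress differently from how she would have described it an hour earlier. That difference would be an effect of allocation recorded as a baseline value. It would then enter every analysis that subtracts T0 or contrasts arms over time.

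Two further problems follow from the same ordering:

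- **Consent.** It is the trigger for assignment in one section and appears after assignment in another. Both cannot be right.
- **Missing T0.** Someone who is assigned but never attends T0 is a randomised participant without a baseline. The rule of counting lost participants as unchanged has no value to start from.

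The pilot is meant to estimate effect sizes and inform a larger trial, so a distorted change score would be carried into that trial's planning.

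**Working it through.** **1. The order of steps, read from the text**

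| Step | Randomisation | VR arm section | Assessment / Figure 2 |
|---|---|---|---|
| Written consent | before the envelope | described at the briefing of assigned participants | not addressed |
| Envelope opened | once the participant consents | already done | not addressed |
| T0 survey | not mentioned | before the introduction to VR, around the briefing | before the intervention |
| Arm known to participant | yes | yes (invited as an assigned participant) | not addressed |

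For VR, the wording puts assignment before T0. For audio and waitlist, the envelope rule applies to all arms and no survey is placed ahead of it, so the same order is inferred. No readable text puts T0 before the envelope.

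**2. Inputs for the size of the consequence**

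- From the protocol (Target group): 90 participants, 3 × 30 = 90, so n = 30 per arm. Effect sizes from earlier studies: 0.4 to 0.54.
- Assumed, because the protocol gives no figures: SD 1 at T0 and T1; T0-T1 correlation ρ = 0.6, with a range of 0.5 to 0.7; two-sided 5% test; a shift b of 0.1, 0.2 or 0.3 SD in one arm's T0 only; no true treatment effect.

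**3. Change-score comparison**

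The bias in the between-arm change, and in the T0-T1 group-by-time term, equals b in size.

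- SD of change = √(2(1 − ρ)) = √0.8 = 0.894
- SE of the difference = 0.894 × √(2/30) = 0.894 × 0.258 = 0.231
- Rejection rate = 1 − Φ(1.96 − b/SE) + Φ(−1.96 − b/SE)

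| b (SD) | b/SE | Type I error, normal approximation, ρ = 0.6 | Simulated t-test (20,000 replicates), ρ = 0.6 | Range for ρ = 0.5 to 0.7, normal approximation |
|---|---|---|---|---|
| 0.1 | 0.43 | 7.2% | 7.1% | 6.7% to 7.9% |
| 0.2 | 0.87 | 13.9% | 13.3% | 12.1% to 17.0% |
| 0.3 | 1.30 | 25.5% | 24.6% | 21.3% to 32.3% |

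Set against the cited effects, b/0.4 is 25%, 50% and 75%; b/0.54 is 19%, 37% and 56%.

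**4. Baseline-adjusted comparison**

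The bias is ρb, with SE = √(1 − ρ²) × √(2/30). For ρ = 0.5 to 0.7:

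| b (SD) | Bias (SD) | Type I error |
|---|---|---|
| 0.1 | 0.05 to 0.07 | 5.6% to 6.7% |
| 0.2 | 0.10 to 0.14 | 7.3% to 11.8% |
| 0.3 | 0.15 to 0.21 | 10.3% to 20.7% |

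Adjustment reduces the bias but does not remove it.

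**5. Post-test scores alone**

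A between-group t-test on T1 scores does not use T0, except for participants whose missing T1 is set to no change.

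**6. After re-ordering**

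If T0 is complete before the envelope is opened, allocation cannot move it. Then b = 0 in expectation, and so is the bias in steps 3 to 5. The sample size stays at 90.

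**The case against.** The strongest reply is that the order is read into the text. The sentence about the pre-test survey shows, on its own, only that T0 precedes the introduction to VR. It also mentions consent, which the Randomisation section has already used as the trigger for assignment. The sentence may therefore be a loose recap of earlier steps and not a chronology. Figure 1, the CONSORT diagram, is not readable in the copy reviewed and could place T0 first. In addition, this is a small pilot with unblinded participants and self-reported outcomes, so expectation can affect T1 and T2 whatever the order at T0.

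Much of this stands, and it limits what can be claimed:

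- A reader might infer that T0 after allocation is explicit in all three arms. It is explicit only in the VR text; for audio and waitlist it is an inference.
- A reader might infer that the waitlist T0 happens in a different setting, since that group is one "who will not attend any briefing session". The Assessment section and Figure 2 give the same mode and site for everyone; only the attached briefing is absent.
- A reader might infer that the shift would imitate a benefit. Its direction is unknown, and it could equally hide one.
- A reader might take arm-dependent non-attendance at T0 as expected. Nothing in the protocol shows that it will occur.

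The reply does not remove the point. If the sentence is a recap, the wording still has assigned participants consenting and completing T0 in connection with their briefing. If Figure 1 puts T0 first, it conflicts with the text. Expectation effects at follow-up are no reason to allow a further, avoidable one at baseline.

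**Conclusion.** The point holds in this form: followed as written, the readable text lets T0 be answered with the arm known, and it contradicts itself on whether consent comes before or after assignment. If allocation knowledge shifts T0 in one arm by 0.1, 0.2 or 0.3 SD, the pre-post change and the group-by-time contrast are biased by that amount. At a correlation of 0.6 and 30 per arm, the type I error of the change comparison is then about 7%, 13% and 25%. Baseline adjustment lowers the bias to the correlation times the shift. A comparison of observed post-test scores alone does not carry it.

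The shifts and the correlation are assumptions with no support in the protocol, so these figures show sensitivity and do not forecast the trial's error rate. The conclusion about order rests on the text without Figure 1. The defect deserves correction before enrolment because a baseline taken after allocation cannot be repaired in the analysis.

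**What to change.** State one order for all three arms in Randomisation, in the VR arm section and in Assessment:

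1. eligibility confirmed;
2. written consent;
3. T0 survey completed;
4. next envelope opened;
5. briefing (VR and audio) or waitlist.

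Say explicitly that no envelope is opened until T0 is complete. Remove consent and the pre-test survey from the description of the VR briefing, and make Figure 1 show the same sequence. With this order the T0 interviewer cannot know the arm, and everyone randomised has a baseline, so the rule for lost participants always has a starting value.

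The cost is small. The steps, instruments, site and sample size do not change. Allocation and, for the two active arms, the briefing come slightly later in the same visit.

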#### **B) Audio-based MBI group (Control group)**

Participants in the audio-based group will also attend a briefing session where they will receive information on mindfulness practice. They will listen to the same 10-15 minute audio-based MBI instruction as provided in the VR-based MBI app. Similar to the VR-based MBI group, they will receive reminder messages and telephone follow-ups. The only difference between the VR-based MBI and audio-based MBI groups will be the absence of VR technology in the audio-based group.

#### **C) Usual care group (Waitlist control group)**

The third group will be the waitlist control group, who will not attend any briefing session or engage in mindfulness-based interventions during the pilot period. Instead, they will receive usual care and services provided by community service centres. No additional or new intervention will be provided to them during the study period. We will provide the VR-based MBI to the waitlist control group participants after they have completed the control period.

